**Design:**

A pragmatic cluster-randomized trial will be conducted to evaluate the CDA's CVD Toolkit. All family physicians in Ontario, Canada were randomly allocated to receive the Toolkit, which includes several printed educational materials targeting CVD screening, prevention and treatment, either in spring 2009 (intervention arm) or in spring 2010 (control arm). Randomization occurred at the level of the practice. Forty family physicians from each arm will be recruited to participate, and the medical records for 20 of their diabetic patients at high risk for CVD will be retrospectively reviewed. Outcome measures will be assessed for each patient between July 2009 and March 2010. The primary outcome will be that the patient is receiving a statin. Secondary outcomes will include 1) the receipt of an angiotensin converting enzyme inhibitor or angiotensin receptor blocker, 2) various intermediate measures (A1c, blood pressure, LDL-cholesterol, total-/HDL-cholesterol ratio, body mass index and waist circumference), and 3) clinical inertia (the failure to change therapy in response to an abnormal A1c, blood pressure or cholesterol reading). The analysis will be carried out using multilevel hierarchical logistic regression models to account for the clustered nature of the data. The group assignment will be a physician-level variable. In addition, a process evaluation study with six focus groups of family physicians will assess the acceptability of the CDA's Toolkit and will explore factors contributing to any change or lack of change in behaviour, from the perspectives of family physicians.

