### Study participants

From the Toolkit's mailing lists, we will randomly select Ontario family physicians to approach about participating in a primary data abstraction study. Physicians will be contacted by fax with a brief synopsis of the study purpose and the planned data abstraction. They will be invited to accept or decline to participate by fax or telephone. Follow-up telephone calls will be made to physicians who do not respond. We will recruit 40 family physicians from each of the intervention and control arms. For practical reasons, the recruited physicians will practice within 150 km of the study centre, which incorporates both urban and rural areas. In order to increase the likelihood that the participating physicians are representative of typical practitioners and are not self-selected towards good performers with an interest in diabetes quality of care, the letter of invitation will not describe the study in detail or what data will be collected.

Individual patients with diabetes seeing each physician will be identified through the physician's billing records or electronic health records. We will randomly select from these records 20 diabetic patients per physician aged = 18 years who were seen in the office at least once between July 2009 and March 2010, and who fulfill the Clinical Practice Guidelines' definition of being at "high risk for CV events": [18]

• Men aged ≥ 45 years, women aged ≥ 50 years; or

• Men aged < 45 years and women < 50 years with at least one of the following:

• Macrovascular disease (silent myocardial infarction, or evidence of peripheral arterial, carotid arterial or cerebrovascular disease)

• Microvascular disease (nephropathy or retinopathy)

• Family history of premature coronary or cerebrovascular disease in a first-degree relative

• Extreme level of a single risk factor (LDL-C > 5.0 mmol/L, systolic BP > 180 mmHg)

• Duration of diabetes > 15 years with age > 30 years

Patients who were concomitantly seeing endocrinologists will not be specifically excluded from the study. Although such patients may be more likely to have received benefit from the Toolkit since all endocrinologists received the Toolkit in a non-randomized fashion, less than 18% of people with diabetes in Ontario see both endocrinologists and family physicians[21]. Any such patients would bias the results of the study towards the null.

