### Data collection and outcomes

Starting in the spring of 2010, we will perform a retrospective data abstraction from the paper charts and/or electronic health records in each physician's office. For each patient, demographic information (including date of birth, sex and postal code of home residence) and clinical information (including diabetes duration, comorbidities, family history and baseline drug utilization) will be collected. Outcome measures will be assessed for each patient for the period between July 2009 and March 2010. The primary outcome will be that the patient is receiving a statin (as determined by the record of a new prescription, the record of a prescription renewal, or a notation that the patient is taking a statin). This outcome is selected because as a process of care outcome, it is closely linked to physicians' behaviour and hence is more likely to change as a result of the intervention, and because no more than one-third of patients currently receive statins, [13,22,23] so there is substantial opportunity for improvement.

The other process outcome that will be evaluated is whether the patient is receiving a prescription for an angiotensin-converting enzyme inhibitor or angiotensin receptor blocker. In addition, the following intermediate outcomes will also be collected:

• A1c

• Blood pressure

• LDL-cholesterol

• Total-/HDL-cholesterol ratio

• Body mass index

• Waist circumference

When there are multiple measurements for these intermediate measures for a patient, the last one during the observation period will be used.

We will also measure "clinical inertia"[24]. For each A1c, blood pressure or LDL-cholesterol reading that is above the recommended clinical practice guideline target, we will determine whether, at the next patient visit, there is notation in the chart of a recommended change: the addition of a new medication, a dose change for an existing medication, a dietary or physical activity recommendation, etc.

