### Planned analyses

We hypothesize that patients whose family physicians are in the intervention arm will have greater use of appropriate medications and better achievement of targets than patients whose family physicians are in the control arm. The analysis to test this hypothesis will be carried out using multilevel hierarchical logistic regression models to account for the clustered nature of the data, i.e., patients clustering within physicians and the attendant reduction in statistical independence. The group assignment will be a physician-level variable.

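### Clinical inertia is scored only at the visit after the reading, so a same-day response to a high office blood pressure goes uncounted and a Toolkit effect on same-visit action is diluted

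*Protocol article*

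**What the plan says.** The Abstract (Design) lists among the secondary outcomes "clinical inertia (the failure to change therapy in response to an abnormal A1c, blood pressure or cholesterol reading"). It says nothing about when the change must occur.

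Data collection and outcomes turns this into a scoring rule. The trigger is the same for all three measures: "For each A1c, blood pressure or LDL-cholesterol reading that is above the recommended clinical practice guideline target". The response is then sought at one point only: "we will determine whether, at the next patient visit, there is notation in the chart of a recommended change". What counts as a response is broad: "the addition of a new medication, a dose change for an existing medication, a dietary or physical activity recommendation, etc".

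The source is "retrospective data abstraction from the paper charts and/or electronic health records in each physician's office", and the period is fixed: "Outcome measures will be assessed for each patient for the period between July 2009 and March 2010". Under Study participants, patients qualify if they are among those "who were seen in the office at least once between July 2009 and March 2010", so a second visit in the period is not guaranteed.

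Nowhere does the article credit a change charted at the visit where the reading was taken, or treat blood pressure differently from the laboratory tests.

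**The concern.** The next-visit rule suits A1c and LDL-cholesterol, because those results usually arrive after the patient has left. It does not suit a blood pressure taken in the office, which the physician sees at once. If a drug is added or a dose changed that day, the rule as written gives no credit. The reading is scored as inertia unless a further change is charted at the following visit. Where the first change brought the pressure to target, no further change is needed, so a prompt and successful response can be recorded as a failure.

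The error is not neutral between arms if the Toolkit works in the consultation, as its algorithm card and patient sheets may. More same-visit action in the intervention arm means more uncounted responses there. That works against the direction the article expects, namely that "patients whose family physicians are in the intervention arm will have greater use of appropriate medications and better achievement of targets". Blinding the abstractor does not help, because the error lies in the rule and not in the assessor.

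**Working it through.** The article states no figure for clinical inertia, so there is none to reproduce. The check is misclassification algebra for the blood pressure component.

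**Inputs from the article:** the trigger, the scoring visit, the observation period and the one-visit minimum, as set out above.

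**Inputs assumed (none is in the article):**
- s = probability of a charted change at the visit of the high reading
- a = probability of a charted change at the next visit if nothing was done at the reading visit
- b = probability of a further charted change at the next visit after same-day action

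**Formulas:**
- Inertia with same-day action credited (true): (1-s)(1-a)
- Inertia as the rule is written (scored): (1-s)(1-a) + s(1-b)
- Overstatement in each arm: s(1-b), which is never negative
- Difference, Toolkit (T) minus control (C): scored = true + [sT(1-bT) - sC(1-bC)]

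If a and b are the same in both arms, these reduce to true = -(sT-sC)(1-a) and scored = (sT-sC)(a-b). The share of the true difference that survives is (b-a)/(1-a), which is below 1 whenever b is below 1. An effect confined to same-visit action is therefore lost if b = a, reversed if b < a, and attenuated if b > a.

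**Control arm, s = 25%, a = 15%, b = 10%:**
- True: 0.75 × 0.85 = 63.75%
- Scored: 63.75% + 0.25 × 0.90 = 86.25%

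**Toolkit arm under three assumptions:**

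| Toolkit raises | s, a, b | True inertia | Scored inertia | True difference | Scored difference |
|---|---|---|---|---|---|
| s only, +10 | 35, 15, 10% | 0.65 × 0.85 = 55.25% | 55.25 + 35 × 0.90 = 86.75% | -8.5 | +0.5 |
| s +10, a and b +5 | 35, 20, 15% | 0.65 × 0.80 = 52.00% | 52.00 + 35 × 0.85 = 81.75% | -11.75 | -4.5 |
| s, a and b all +10 | 35, 25, 20% | 0.65 × 0.75 = 48.75% | 48.75 + 35 × 0.80 = 76.75% | -15.0 | -9.5 |

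**Range when the Toolkit raises s alone and b ≤ a.** The pairs (a, b) are (15, 10), (20, 10), (15, 15) and (20, 5)%.
- A 10-point rise in s, starting from 15, 25 or 35%: true difference -8.0 to -8.5, scored 0.0 to +1.5.
- A 5-point rise in s (25% to 30%): true difference -5 × 0.80 = -4.0 to -5 × 0.85 = -4.25; scored 5 × 0 = 0 to 5 × 0.15 = +0.75.
- Overstatement of the level across the 10-point cases: from 0.15 × 0.85 = 12.75 points to 0.45 × 0.95 = 42.75 points.

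**A case with b > a.** With s = 20% vs 30%, a = 30% and b = 50%, the true difference is -10 × 0.70 = -7 points and the scored difference is 10 × (0.30 - 0.50) = -2 points: attenuated, with the right sign.

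**The case against.** A reader might infer that the rule erases or reverses a real Toolkit effect on inertia, so that the trial could report harm where response improved. The documents do not support that as a general statement. In the cases above, loss or reversal appears only when two conditions hold together: the Toolkit changes same-visit action alone, and b does not exceed a. Neither is given in the article. Diet or activity advice counts as a response, so b need not be low. The card and patient sheets can prompt action at any visit, so a and b may rise as well. The scored effect then keeps its sign.

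A reader might also infer that the Abstract and the Methods contradict each other. They do not: the Abstract names a concept and is silent on timing. The fault is that the Methods rule misses part of that concept.

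Other limits stand. The article does not say where blood pressure is measured, nor that it is the most frequent of the three readings. It gives closeness to physician behaviour as the reason for choosing the statin outcome, not for inertia. For the laboratory tests the rule is broadly suitable.

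What the objection does not remove is the rule itself. It names the scoring visit, so this is not a detail left to a fuller document, and nothing else in the article credits a same-day change.

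**Conclusion.** The point holds for the blood pressure component of one secondary outcome. Followed literally, the rule scores a same-day response to a high office blood pressure as inertia unless a further change follows. It overstates blood pressure inertia in both arms by s(1-b) and dilutes any Toolkit effect on same-visit action. Under the assumed rates, the distortion runs from attenuation (-15.0 true, -9.5 scored) to loss or slight reversal (-8.5 true, +0.5 scored).

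The conclusion that same-day action goes uncounted rests on the text and on the inference that office blood pressure is known at the visit. The size and sign of the effect on the arm contrast rest wholly on assumed rates and should be read as illustration. The primary statin outcome and the sample size do not depend on this rule. It should be corrected before abstraction, but it does not threaten the trial's main conclusion.

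**What to change.** In Data collection and outcomes:

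1. Count a recommended change noted at any time from the visit or date of the reading up to and including the next patient visit.
2. State how readings with no later visit between July 2009 and March 2010 are scored. A workable rule is to score blood pressure on the reading visit alone and to treat laboratory readings as not scorable.
3. Report inertia separately for blood pressure, A1c and LDL-cholesterol, since the timing problem differs between them.

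The abstraction form should carry the date of each reading and of each charted change. The window should not start from the date a laboratory result reached the office, because charts may not record it.

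The cost is a few sentences and two date fields. Abstraction is retrospective and starts in spring 2010, so no extra patients or visits are needed. The downside is that the longer window will catch a few changes not prompted by the reading.

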### Proposed sample size

We will power the study to be able to detect an absolute 10% difference in statin prescription rates between groups, a threshold similar to the median effect size found in a systematic review of printed educational materials[25]. Even this modest improvement would be an important achievement at a population level. To have 80% power to detect this difference with alpha-error of 0.05, a sample size of 408 per group would be needed. However, this sample size must be inflated by a variance inflation factor (VIF) to ensure adequate power when taking clustering into account using generalized estimating equation models[26]. The VIF is given by VIF = 1 + (*n*-1) × ρ, where *n *is the mean cluster size and ρ is the intraclass correlation coefficient, a measure of the degree of correlation of the outcome within clusters. Previous data have shown that ρ for appropriate statin use by diabetic patients clustered within primary care physicians is 0.05[27]. If we assume a cluster size of 20 eligible patients per physician (which represents a reasonable number of patients whose data could be abstracted in two days), the VIF is 1 + 0.05 × (20-1) = 1.95, so the actual required sample size is 796 patients in each group, or 40 physicians per group.

### Planned analyses

We hypothesize that patients whose family physicians are in the intervention arm will have greater use of appropriate medications and better achievement of targets than patients whose family physicians are in the control arm. The analysis to test this hypothesis will be carried out using multilevel hierarchical logistic regression models to account for the clustered nature of the data, i.e., patients clustering within physicians and the attendant reduction in statistical independence. The group assignment will be a physician-level variable.

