### Allocation of participants

All family physicians in Ontario were randomized to either the intervention or control group using computer-generated randomization. Randomization occurred at the level of the practice based on the physicians' primary practice address recorded with the College of Physicians and Surgeons of Ontario, so that all physicians practicing at a single location were assigned to the same group. This was done to prevent contamination between physicians in group practices who may share information and resources. The randomization was stratified by health region.

In addition to the randomized distribution to family physicians in Ontario, the Toolkit was also distributed to all endocrinologists in Ontario, and to all family physicians and endocrinologists in all other Canadian provinces and territories in a non-randomized fashion. Endocrinologists will not directly form part of the study.

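### Practices were randomised, but the model and the VIF stop at the physician and no rule keeps recruited physicians in separate practices; the test is anti-conservative if they share one

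*Protocol article*

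**What the plan says.** All places are in the protocol article.

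- **Allocation.** The abstract states "Randomization occurred at the level of the practice". Allocation of participants adds that the practice address was used "so that all physicians practicing at a single location were assigned to the same group", and gives the reason: "This was done to prevent contamination between physicians in group practices who may share information and resources". It also states "The randomization was stratified by health region".
- **Sampling.** Under Study participants, "we will randomly select Ontario family physicians to approach about participating in a primary data abstraction study", and "We will recruit 40 family physicians from each of the intervention and control arms". Physicians must practise within 150 km of the study centre. No limit on the number per practice is given.
- **Sample size.** The intraclass correlation "for appropriate statin use by diabetic patients clustered within primary care physicians is 0.05". With 20 patients per physician this gives a VIF of 1.95, 796 patients and 40 physicians per group.
- **Analysis.** Planned analyses specifies multilevel logistic models for patients within physicians, and "The group assignment will be a physician-level variable". It mentions neither a practice level nor health region.

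**The concern.** The unit that was allocated, the practice, appears in neither the stated model nor the VIF. Two recruited physicians from one address would be analysed as two independently allocated units, although a single random draw placed both of them. Any correlation between their patients is then left out of the standard error of the group effect. The article itself gives a reason to expect such correlation, since it chose practice-level allocation because colleagues share information and resources.

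This is more than a detail left open for an analysis plan. The article names the clustering level and the level of the group variable, and an analysis plan that followed it would carry the mismatch forward. At stake are the interval and the p-value for the primary outcome (receiving a statin), and the claim of 80% power.

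**Working it through.** **1. The plan's own figures.** A two-sided alpha of 0.05, 80% power, a 10-point difference and a continuity correction give 408 per group for 50% versus 60%, and the same for 40% versus 50%. Then:

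- VIF = 1 + (20 − 1) × 0.05 = 1.95
- 408 × 1.95 = 795.6, rounded to 796
- 796 / 20 = 39.8, rounded to 40 physicians

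The figures reproduce. They treat the 40 physicians per arm as independent.

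**2. Adding the practice level.** Let a be the mean number of recruited colleagues at the same address per recruited physician (with m recruited physicians in every practice, a = m − 1). Let ρp be the correlation between patients of different physicians in one practice. Then

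DE = 1 + 19 × 0.05 + 20 × a × ρp = 1.95 + 20 × a × ρp.

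The actual alpha of the two-level test is approximately 2 × [1 − Φ(1.96 × √(1.95/DE))]. Power with 800 patients per arm is Φ(√((800/DE)/408) × (1.96 + 0.84) − 1.96), scaled so that 408 independent patients give 80%.

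**3. Range for a.** The documents give neither a nor ρp. Under random selection of 40 physicians from N eligible physicians per arm, each with c colleagues at the same address, a = c × 39/(N − 1). Assumed pools:

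- N = 2000, c = 5: a = 195/1999 = 0.10
- N = 1000, c = 5: a = 195/999 = 0.20
- N = 500, c = 10: a = 390/499 = 0.78

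**4. Results.**

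| a | ρp | DE | Actual alpha | Power |
|---|---|---|---|---|
| 0 (one per practice) | any | 1.95 | 5.0% | 80% |
| 0.10 | 0.02 | 1.99 | 5.2% | 79% |
| 0.10 | 0.05 | 2.05 | 5.6% | 78% |
| 0.20 | 0.02 | 2.03 | 5.5% | 79% |
| 0.20 | 0.05 | 2.15 | 6.2% | 76% |
| 0.78 | 0.02 | 2.26 | 6.9% | 74% |
| 1 (two per practice) | 0.01 | 2.15 | 6.2% | 76% |
| 1 | 0.02 | 2.35 | 7.4% | 73% |
| 1 | 0.05 | 2.95 | 11.1% | 63% |

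For a = 1 and ρp = 0.02, DE = 1.95 + 20 × 1 × 0.02 = 2.35. The true standard error is √(2.35/1.95) = 1.10 times the planned one, and 408 × 2.35 = 959 patients (48 physicians) per arm would be needed. A simulated t-test on physician means gave an alpha of 7.2% for this case, against 7.4% from the formula.

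The last row is a boundary. There ρp equals the whole within-physician correlation of 0.05, so patients of different physicians in a practice are as alike as patients of the same physician.

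**5. Region.** In simulation with one physician per practice, balanced strata and an assumed region correlation of 0.01, a test that ignores region had an alpha of about 4.1%. That is conservative.

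**The case against.** The strongest reply is that overlap may be rare. Forty physicians per arm are drawn at random from a mailing list of all Ontario family physicians, within a 150 km radius. A mean of two per practice would require each recruited physician to have, on average, a recruited colleague at the same address. If the eligible pool is large, a is near 0.1 and alpha is barely above 5%. If no two recruited physicians share a practice, physician and practice coincide, and the model, the VIF and the description of group are all correct. This stands, and it is why the range must start at no effect. It does not remove the point: the plan does nothing to secure that case, and a small pool, large practices or colleagues accepting together would raise the overlap.

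A second reply is that the sample size has slack. Data collection and outcomes puts current statin use at no more than one-third. From that rate 390 per group suffice with the continuity correction, or 370 without it, instead of 408. Without the correction, power for one-third versus 43.3% is 84% at DE 1.95 and still 80% at DE 2.15. That softens the loss of power but leaves alpha unchanged.

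Three stronger readings are tempting and are not supported:

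- A reader might infer that the type I error does exceed 5%. That depends on an overlap and a correlation that the documents do not give.
- A reader might infer that leaving out health region inflates alpha. It tends to make the test conservative, and adjustment terms are commonly left to an analysis plan.
- The Discussion criticises earlier studies for unit of analysis errors, and a reader might say this plan repeats them exactly. The Discussion does not say which kind it means, and this plan does allow for clustering of patients within physicians.

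**Conclusion.** The mismatch is certain from the text: practices were randomised within health regions, the model and the VIF stop at the physician, and the sampling rule does not make the two levels coincide. Its consequence is conditional. It needs recruited physicians who share practices and a positive correlation between their patients' outcomes. Under the assumed values, alpha runs from 5.0% (no overlap), through about 5.2% to 5.6% (about 0.1 recruited colleagues per physician), to about 7.4% (two per practice, ρp = 0.02). The 11% figure joins heavy overlap with the largest correlation that the plan's own 0.05 allows, and should not be quoted as the expected effect.

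The VIF of 1.95, and the 80% power built on it, hold as calculated only if each recruited physician comes from a different practice, or if colleagues' patients are uncorrelated. This should be fixed because the remedy is nearly free, but the likely harm does not make it a fatal flaw.

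**What to change.** **Preferred.** Add to Study participants that at most one physician, chosen at random, is approached per practice address. Physician and practice then coincide, and the stated VIF and two-level model are valid as they are.

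**Otherwise.** Add a practice-level random intercept (patients in physicians in practices) or use practice-clustered standard errors. Describe group assignment as a practice-level variable, and state under Proposed sample size that the VIF assumes one physician per practice.

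**Secondary, for precision only.** Include the health-region stratum in the model.

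**Cost.** One sentence in the sampling rule, or one or two in the analysis and sample-size sections. Practice address and health region were already used for the randomisation, so no new data are needed. If practices overlap and the model route is taken, the interval becomes somewhat wider, as it should.
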